## Abstract

**Background:**

This trial addresses the global problem of chronic venous leg ulcers (CVLUs), wounds that cause significant infirmity for an estimated 9.7 million people annually, mainly older adults with comorbidities. Advanced therapies are needed because standard topical therapies are often ineffective or yield only short-term wound healing. Thus, we are testing a new oral therapy containing the bioactive elements of fish oil, eicosapentaenoic acid (EPA) and docosahexaenoic acid (DHA), for targeting and reducing the high numbers of activated polymorphonuclear leukocytes (PMN) in wound microenvironments that keep CVLUs “trapped” in a chronic inflammatory state.

**Methods:**

This double-blind RCT will include 248 eligible adults ≥ 55 years of age with CVLUs receiving standard care at a large Midwest outpatient wound clinic. Participants are randomized to two groups: 12 weeks of daily oral therapy with EPA + DHA (1.87 g/day of EPA + 1.0 g/day of DHA) or daily oral therapy with placebo. At 0, 4, 8, and 12 weeks, across the two groups, we are pursuing three specific aims: Aim 1. Compare levels of EPA + DHA-derived lipid mediators, and inflammatory cytokines in blood and wound fluid; Subaim 1a. Compare inflammatory cytokine gene expression by PMNs in blood; Aim 2. Compare PMN activation in blood and wound fluid, and PMN-derived protease levels in wound fluid; Aim 3. Compare reduction in wound area, controlling for factors known to impact healing, and determine relationships with lipid mediators, cytokines, and PMN activation. Subaim 3a. Compare frequency of CVLU recurrence and levels of study variables in blood between the randomly assigned two subgroups (continuing EPA + DHA therapy versus placebo therapy beyond week 12) within the EPA + DHA group with healed CVLUs after 3 months of therapy. Subaim 3b. Compare symptoms of pain at all time points and quality of life at first and last time points across the two groups and two subgroups.

**Discussion:**

This trial will provide new evidence about the effectiveness of EPA + DHA oral therapy to target and reduce excessive PMN activation systemically and locally in patients with CVLUs. If effective, this therapy may facilitate healing and thus be a new adjunct treatment for CVLUs in the aging population.

**Trial registration:**

ClinicalTrials.gov, NCT03576989; Registered on 13 June 2018.

## Background

Chronic venous leg ulcers (CVLUs) are open skin lesions of the lower legs arising in areas affected by venous hypertension that have been present for at least 6 weeks [1]. These common conditions affect 1% of the adult population and 3.6% of people older than 65 years, and the incidence of CVLUs is rising because they mainly occur in older adults with comorbidities, a growing population [2]. These recurring, disabling wounds cause substantial infirmity [3]. Quality of life (QoL) declines due to related pain, reduced mobility, and protracted treatments that cost payers in the United States alone up to $15 billion per year [4].

Multilayer compression bandaging is the gold standard therapy for CVLUs to reduce venous hypertension in the lower extremities implicated in the pathobiology of CVLUs [5]. However, even with compression therapy, the median time to complete healing of uncomplicated CVLUs is reported to be 12 weeks; older (> 6 months) and larger ulcers (> 20 cm^2^) require significantly more time to heal [6]. Other data indicate that nearly 60% of CVLUs remain unhealed after 12 weeks of compression therapy and usually recur [7, 8]. Thus, new therapies to augment compression bandaging and other standard topical therapies are needed to improve CVLU outcomes and help prevent recurrence [9].

The pathobiology of CVLUs also involves high numbers of activated polymorphonuclear leukocytes (PMNs) in venous circulation and ulcer microenvironments that promote unremitting inflammation and delay healing [10–12]. Although PMNs (e.g., neutrophils) are essential for a short time in the first stage of wound healing to fight off potential pathogens [13], sustained high levels of PMNs typically found in CVLU microenvironments are detrimental to healing. Sustained high levels of PMNs lead to excessive amounts of PMN-derived proteases such as human neutrophil elastase that ultimately destroy newly formed tissue and degrade growth factors, receptors, and the extracellular matrix that are essential for healing [10, 11, 14, 15]. Excessive, prolonged levels of PMNs keep ulcers “trapped” in a chronic inflammatory state. Further, high levels of activated PMNs in venous circulation are involved in CVLU onset [9, 16, 17]. As such, reducing excessive PMN activation systemically and locally is expected to resolve inflammation, advance ulcers through subsequent stages of healing, and deter recurrence.

Studies involving cell cultures and animal models of inflammation show that the bioactive omega-3 polyunsaturated fatty acids (PUFAs) contained in fish oil, eiocosapentaenoic acid (EPA) and docosahexaenoic acid (DHA), are metabolized to eicosanoids and other lipid mediators that inhibit PMN migration to inflamed sites and reduce cell synthesis and secretion of pro-inflammatory cytokines involved in recruiting and activating PMNs [18–21]. Some human studies report lower chemotactic responsiveness of PMNs from whole blood after just 4 weeks of EPA + DHA oral therapy in healthy subjects [22, 23]. After ingestion and rapid incorporation into cell membranes, EPA + DHA are metabolized to lipid mediators that are weak chemoattractants for PMNs. Increasing EPA + DHA levels has also been shown to reduce levels of arachidonic acid (an omega-6 PUFA) that is metabolized to lipid mediators that upregulate pro-inflammatory cytokine synthesis [24–26]. Moreover, there is evidence that EPA + DHA decrease the actual gene expression of pro-inflammatory cytokines in cells by blocking nuclear factor kappa B activity [27, 28]. Specific to wounds, our early pilot work demonstrated that EPA + DHA oral therapy can push an EPA + DHA lipid mediator profile in acute human wound microenvironments that is associated with declining levels of myeloperoxidase, a biomarker of PMN activation [29]. In addition, data from our more recent study showed that EPA + DHA reduces PMN activation in blood and wound fluid [25], and reduces levels of proinflammatory cytokines in venous circulation of patients with CVLUs [30] after 4 and 8 weeks of therapy. While these prior studies have made notable scientific contributions, there is a critical need to expand understanding of the physiological processes responsible for the link between EPA + DHA oral therapy, reduced PMN activation, and CVLU pathobiology.

Therefore, this double-blind randomized controlled trial (RCT) will include 248 eligible adults with CVLUs, randomized to two groups: 12 weeks of daily oral therapy with EPA + DHA (1.87 g/day of EPA + 1.0 g/day of DHA) or daily oral therapy with placebo. At 0, 4, 8, and 12 weeks, across the two groups, we are pursuing three specific aims: Aim 1. Compare levels of EPA + DHA-derived lipid mediators, and inflammatory cytokines in blood and wound fluid; Subaim 1a. Compare inflammatory cytokine gene expression by PMNs in blood; Aim 2. Compare PMN activation in blood and wound fluid, and PMN-derived protease levels in wound fluid; Aim 3. Compare reduction in wound area, controlling for factors known to impact healing, and determine relationships with lipid mediators, cytokines, and PMN activation. Subaim 3a. Compare frequency of CVLU recurrence and levels of study variables in blood between randomly assigned two subgroups (continuing EPA + DHA therapy versus placebo therapy beyond week 12) within the EPA + DHA group with healed CVLUs after 3 months of therapy. Subaim 3b. Compare symptoms of pain at all time points and quality of life at first and last time points across the two groups and two subgroups. The findings are expected to close a significant gap in knowledge about the potential for EPA + DHA oral therapy, as an adjunct to compression therapy, to facilitate healing and prevent recurrence of CVLUs. Our organizing clinical hypothesis is that increasing EPA + DHA intake with oral supplementation will expedite CVLU healing and prevent recurrence by raising levels of EPA + DHA-derived lipid mediators and lowering levels of pro-inflammatory cytokines that will reduce PMN activation systemically and in the wound microenvironment. This research is expected to make a positive impact on individuals, families, and caregivers affected by CVLUs because if EPA + DHA therapy reduces chronic excessive PMN activation, improves healing outcomes and helps prevent recurrence, the significant emotional and financial burdens associated with the pain, social isolation, lost productivity, and protracted health care visits will be reduced.

## Methods

### Design and ethical considerations

This ongoing trial uses a prospective two-group, double-blind, randomized, repeated-measures, placebo-controlled design. Participants are studied at 0, 4, 8, and 12 weeks after eligibility screening, written informed consent, and enrollment to the study. A subset of participants in the EPA + DHA group with healed CVLUs by 12 weeks will be studied for an additional 3 months so that we can determine the frequency of CVLU recurrence. The trial was approved by the local institutional review board of the participating medical center (The Ohio State University [OSU] Wexner Medical Center – July 20, 2018). Figure 1 and Table 1 show the study flow chart and the schedule, respectively.

**Fig. 1 Fig1:**
[figure not shown]
Study flow chart

**Table 1 Tab1:** Study schedule

Time point	Pre-Visit	Visit 1 (Week 0)	Visit 2 (Week 4)	Visit 3 (Week 8)	Visit 4 (Week 12)	Visit 5* (3 mos. Post Week 12)
Enrollment						
Screening	X					
Informed consent		X				
Allocation		X				
Interventions						
Treatment (EPA + DHA)		X	X	X	X	X
Placebo (mineral oil)		X	X	X	X	
Assessments						
Wound treatments	X	X	X	X	X	X
Adherence			X	X	X	X
Biological measures						
Blood and wound fluid		X	X	X	X	X
Fatty acids		X	X	X	X	X
n-3, n-6 lipid mediators		X	X	X	X	X
Cytokines		X	X	X	X	X
PMN activation		X	X	X	X	X
Proteases (wound fluid only)		X	X	X	X	X
Wound area (if wound is present)		X	X	X	X	X
Body mass index		X	X	X	X	X
CEAP		X	X	X	X	X
Revised VCSS (includes pain score)		X	X	X	X	X
Interview/self-report						
Sociodemographic Questionnaire		X				
Perceived Stress Scale		X	X	X	X	X
Health history		X				
Food frequency Questionnaire		X			X	X
VEINES-QoL/Sym Questionnaire		X			X	X

Legend: X = Collected at the given time point. n-3 = Omega 3; n-6 = Omega 6; PMN = polymorphonuclear leukocytes; CEAP = Clinical, Etiologic, Anatomic, and Pathophysiologic classification; VCSS = Venous Clinical Severity Score; VEINES-QoL/Sym = VEnous Insufficiency Epidemiological and Economic Study – Quality of Life/Symptoms. *All assessments at visit 5 are for participants initially randomized to the treatment group, have healed wounds by visit 4, and are consented for the additional study. At visit 4, these participants will be re-randomized to the treatment group or placebo group and have one more study visit, 3 months following visit 4

### Setting

We are recruiting participants over a 53-month period from a pool of patients diagnosed with CVLUs who are receiving treatment with standard single- or multi-layer compression bandaging at the OSU Comprehensive Wound Center (CWC). The study visits occur at the OSU Clinical Research Center, located on the medical center’s main campus.

### Eligibility criteria

Patients are eligible for the study if they are women and men ≥ 55 years of age (1) with a CVLU between the ankle and knee that has been present for at least 4 weeks, but not longer than 12 months, are prescribed compression therapy with 1–4 layer bandaging; (2) with an ankle brachial pressure index (ABPI) between 0.7 and 1.2; (3) with a target wound area of 2–60 cm^2^, (4) who can read and understand English or Spanish, and (5) who can provide consent. Patients are included after full, understandable, and neutral explanation by the project manager or principal investigator (PI) and after giving written informed consent. Patients are excluded when they report a fish allergy or when they receive a treatment or have a condition known to seriously impair normal wound healing (e.g., corticosteroids, selective COX-2 inhibitors, non-steroidal anti-inflammatory drugs >2x/week (exception: aspirin 81 mg/day), chemotherapy, autoimmune diseases, diabetes if HbA1c > 12%, or a venous leg ulcer complicated by cellulitis, exposed tendon or bone).

### Sample size

Sample size was determined to have sufficient power to detect intervention effect on wound healing, the optimal outcome of the study. Using mixed-effects linear modeling for repeated measures, a total of 248 participants (124 per group) are needed to have 80% power to detect an effect size of 0.4 for between-group comparisons in percent wound area reduction. We assumed (1) a first-order autoregressive covariance structure among the three post-intervention repeated measures, (2) a within-subject correlation of 0.7, and (3) an attrition rate of 20% in the sample size calculation. These assumptions are reasonable based on data from our pilot study [25]. The effect size of 0.4 is corresponding to an average of 16% between-group difference in percent wound area reduction with a common standard deviation of 0.4. Our power analysis also applied Bonferroni method to adjust for three comparisons of primary interest (4-week vs. baseline, 8-week vs. baseline, and 12-week vs. baseline). We used the same approach to conduct power analysis for other outcomes. Our sample size will have over 90% power to detect intervention effects on levels of lipid mediators and inflammatory cytokines and PMN activation, which had medium to large effect sizes based on our pilot study [25, 29]. A two-sided significance level of 0.05 was used for all power analyses. Based on OSU CWC data, we will be able to recruit the required number of people (*n* = 248) in the 53-month recruitment period, averaging 4–5 per month.

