### Statistical analysis

Congruent with the RCT design of the study, we will conduct an intent-to-treat analysis. We will first use descriptive statistics to check data distribution, identify outliers, guide appropriate data transformation if needed, and summarize sample characteristics. Two-sample *t* tests and Chi-square statistics will be used to check the balance of baseline measures between two study arms. Mixed-effects linear modeling for repeated measures will be used to test the intervention effect on each outcome measure (PMN activation, lipid mediators, inflammatory cytokines, inflammatory cytokine gene expression, percent reduction in wound area, and pain and QoL). In each model, we will include fixed-effects of treatment (EPA + DHA vs. control), time, and treatment by time interaction, adjusting for possible covariates (e.g., lipid-lowering medications) and data dependancy from repeated measures. From the mixed-effects modeling, we will derive the between-group contrast (EPA + DHA vs. control) estimates of change from baseline in outcome variable at each follow-up time point. Multiple comparison adjustment (e.g., Bonferroni adjustment) will be applied to these between-group contrasts to avoid inflated type I error. Logistic regression modeling will be used to analyze wound recurrence. Again, we will estimate between-group difference in the risks of wound recurrence, adjusting for potential covariates and multiple comparison. Lastly, we will use longitudinal mediation modeling [39] to test hypothesized mediating pathways. A significant mediation pathway is indicated if both paths from X (e.g., treatment) to M (mediator, e.g., pro-inflammatory cytokine) and from M to Y (e.g., PMN activation) are statistically significant. Adequate model fit of a mediation model will be indicated with a non-significant Chi-square statistic, comparative fit index, and Tucker & Lewis Index ≥ 0.9, and a root mean square error of appromixation of ≤ 0.08 [40]. The effect of biological sex and its interaction with treatment will also be examined in the regression models. Missing Data. We expect missing data due to non-adherence, loss of follow-up, or lack of data due to healed wounds. We will carefully examine the extent and pattern of missing data. We will use an indicator variable to flag missing data due to healed wounds and incoporate the variable in the missing pattern analysis. Mixed-effects modeling allows for missing at random [41]. If missing completely at random (MCAR) exists, multiple imputation will be used in order to use the optimal amount of information in our analysis. For missing not at random, pattern-mixture modeling will be used [42]. We will also conduct sensitivity analysis to examine the robustness of study findings from different methods. The trial is considered “minimal risk” by the local IRB and therefore no interim analysis or formal plans for stopping the trial are planned. In terms of data and safety monitoring, a Safety Officer (SO) has been selected and approved by the funding agency in consultations with the PI. The SO has no financial, scientific, or other conflict of interest with the trial. The SO meets with the PI twice annually to review study progress, data quality, and participants’ safety.

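### The 80% power figure fits a treatment difference averaged over weeks 4, 8 and 12, but the planned Bonferroni-adjusted tests are visit by visit and have about 66–74% power each for the same effect

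*Protocol article*

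**What the plan says.** The Sample size section of the protocol article states that "a total of 248 participants (124 per group) are needed to have 80% power to detect an effect size of 0.4". The outcome it sizes the trial on is percent wound area reduction. It lists three assumptions: first "a first-order autoregressive covariance structure among the three post-intervention repeated measures", then "a within-subject correlation of 0.7", and last "an attrition rate of 20% in the sample size calculation". It translates the effect into points, taking the standard deviation to be 0.4 as well: "The effect size of 0.4 is corresponding to an average of 16% between-group difference in percent wound area reduction with a common standard deviation of" that size. It adds that "Our power analysis also applied Bonferroni method to adjust for three comparisons of primary interest", and lists these as weeks 4, 8 and 12, each against baseline. Significance is two-sided at 0.05.

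The Statistical analysis section fits a mixed-effects model with treatment, time and their interaction. It then derives between-group contrasts as "estimates of change from baseline in outcome variable at each follow-up time point", with a multiple-comparison adjustment for which Bonferroni is the example given. It names no contrast averaged over visits.

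**The concern.** Averaging three correlated measurements reduces the variance, so an averaged contrast is more powerful than a contrast at one visit. If the sample size took that gain while the analysis tests each visit separately, each planned test has less power than the article states. The three comparisons described as being of primary interest are those visit contrasts. A non-significant result at one of them would then be read against a power of 80% that the test did not have.

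**Working it through.** **Inputs (Sample size section).** 124 per arm; 20% attrition, so 124 × 0.8 = 99 evaluable per arm; d = 0.16/0.4 = 0.4; AR(1) correlation 0.7 over three post-baseline visits; two-sided alpha 0.05/3 = 0.0167.

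**Step 1: reproduce 248.** The variance of the mean of three AR(1) measures, relative to one measure, is

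[3 + 2(0.7 + 0.7 + 0.49)]/9 = 6.78/9 = 0.753.

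With n per arm = 2 × 0.753 × (z for 1 − 0.0167/2 + z for 0.80)²/0.4², the normal approximation gives 99 evaluable per arm. Then 99/0.8 rounds up to 124 per arm, or 248 in total, an exact match. Power at 99 per arm is 80.2% (79.5% with the noncentral t).

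**Step 2: other readings.**

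| Contrast | Alpha | Total N |
|---|---|---|
| Simple average, AR(1) | 0.05/3 | 248 |
| Optimally weighted average, AR(1) | 0.05/3 | 244 |
| Average, equal correlations | 0.05/3 | 264 |
| Average, AR(1) | 0.05 | 186 |
| Single visit | 0.05/3 | 328 |
| Single visit | 0.05 | 248 |

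The last row also gives 248, but it makes no use of the correlation inputs and omits the Bonferroni step that the article says was applied.

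**Step 3: power of the planned visit contrast.** At one visit the variance factor is 1. With d = 0.4 at that visit and alpha 0.05/3:

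- Full 20% loss at that visit (99 per arm): 66.3% by the normal approximation, 65.5% by the noncentral t.
- Gradual loss, assuming retention of 93%, 87% and 80% at weeks 4, 8 and 12, with partial data used through the AR(1) model: 74%, 72% and 69%.
- No loss (124 per arm): 77.5% by the normal approximation, 77.0% by the noncentral t.

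The effect detectable with 80% power at 99 per arm is d = 0.46. By the noncentral t it is 0.463, and 0.463 × 0.4 = 0.185, or 18.5 points instead of 16. To have 80% power at each visit for d = 0.4, 131 evaluable per arm are needed: 131/0.8 rounds up to 164 per arm, or 328 in total.

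**Step 4: dependence on the shape of the effect.** These figures use 99 per arm, alpha 0.05/3 and the normal approximation. All three shapes average 0.4.

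| Effect at weeks 4 / 8 / 12 | Power at each visit | At least one visit |
|---|---|---|
| 0.4 / 0.4 / 0.4 | 66% / 66% / 66% | 85% |
| 0.3 / 0.4 / 0.5 | 39% / 66% / 87% | 90% |
| 0.2 / 0.4 / 0.6 | 16% / 66% / 97% | 97% |

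With the flat effect, power for all three visits to be significant is about 46%.

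**The case against.** The strongest reply is that nothing in the Sample size section is miscalculated. It describes the 16 points as an average, and 248 follows exactly from the stated inputs on that reading. That stands: the fault is a mismatch between the quantity that was powered and the tests that are planned.

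The averaged basis is also an inference, because the article never says time-averaged and a single unadjusted visit gives 248 too. That stands as well. The shortfall does not depend on it, since under either origin of 248 an adjusted visit contrast with d = 0.4 and 99 per arm has about 66% power.

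The figure of 66% is a floor. It removes all 20% from every visit and gives the mixed model no credit for partial data. The article gives Bonferroni only as an example in the analysis. With a flat effect of 0.4 and 99 per arm, Holm would give about 73–74% per visit and Hochberg about 75–76%, before any gain from partial data. Covariate adjustment could help too: if covariates explained 25% of the variance, which is an assumption, power per visit would be about 80%. These points justify a range, but the article claims none of these gains in its power statement.

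A reader might go further and infer that the trial is underpowered overall, or that week 12 in particular is compromised. The documents do not support either. With a flat 0.4 effect the chance of at least one significant visit is about 85%. If the effect grows over time and still averages 0.4, week 12 exceeds 80% and week 4 is the weak visit. Growth patterns that only reach 0.4 at week 12 do give lower power, but they average less than 0.4 and so depart from the article's own assumption. Nor does the article rank week 12 above weeks 4 and 8; it lists the three together.

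**Conclusion.** The point holds as a mismatch between the stated power and the planned tests. The 80% is reproduced for the difference averaged over three visits, while the multiplicity-adjusted tests are the separate visit contrasts. If the difference is 0.4 at a visit, that visit's contrast has about 66% power with the full 20% attrition at that visit, and about 69–74% under the assumed gradual dropout. Even with complete follow-up it has 77%. It does not reach 80% under Bonferroni without a further assumption, such as a gain from covariates. The result rests on the article's own effect size, standard deviation, correlation, attrition and alpha. Only the retention pattern is assumed.

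**What to change.** One of two wording changes would align the sections:

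1. State in Sample size that 80% refers to the treatment effect averaged over weeks 4, 8 and 12. In Statistical analysis, make that averaged contrast the primary test of percent wound area reduction, with the visit contrasts supportive.
2. Keep the three Bonferroni-adjusted visit contrasts and restate power as about 66–74% per contrast, with the dropout assumption given. Add that 99 per arm gives 80% power per visit for d of about 0.46 (18.5 points).

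Naming a single visit, for example week 12, as the only test at two-sided 0.05 would also give 80% with 248. That would drop two of the comparisons now called primary, and it is a choice for the sponsor.

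None of these needs more participants. The cost is that the individual visits lose confirmatory status (option 1, or all but the chosen one under a single-visit test), or that the stated power becomes less favourable (option 2). The Trial status section reports nine participants enrolled, so at that point the change could still be made well before most outcome data accrue.
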